## Abstract

Premature, non-physiological tooth wear in childhood has numerous repercussions for oral health. This is a growing problem with multifactorial causes and associated with the current lifestyle. The introduction of new concepts and indices is crucial for enhancing the understanding and management of dental conditions. In this context, we present the Childhood Early Oral Aging Syndrome (CEOAS) and the associated index, which aim to assess early enamel wear in the primary dentition. Rather than focusing solely on isolated etiologies, the index proposes a comprehensive evaluation of signs and symptoms, considering various factors that contribute to the premature and non-physiological loss of dental structure, including wear of both intact and hypomineralized enamel. Indices that evaluate the main factors of early oral aging in childhood and their interactions are fundamental for understanding the condition and developing effective control and treatment strategies, particularly given that there is currently no global index encompassing this information. The aim of the present study was the development and determination of content validity of the Childhood Early Oral Aging Syndrome (CEOAS) index for the primary dentition as a diagnostic and epidemiological survey tool.

**Trial registration**: ClinicalTrials.gov ID: NCT06378385.

## Introduction

The increase in premature, non-physiological tooth wear in childhood has numerous repercussions for oral health. This constitutes a growing phenomenon associated with multifactorial causes and the current lifestyle. With more in-depth knowledge on dental caries and its control, new demands emerge that need to be recognized by healthcare providers to ensure prevention as well as the control of the disease and etiological factors [1].

Non-carious diseases lead to progressive, irreversible dental structure loss, with initial causes unrelated to bacterial involvement [2]. Tooth wear, influenced by age, encompasses erosion, attrition, and abrasion, resulting in varying degrees of structure loss. Pathological tooth wear, marked by unacceptable levels of wear, can cause sensitivity and impact aesthetics and function [3]. The rising prevalence of non-carious oral issues underscores the need for improved practices, health education, research, training, and a transdisciplinary approach [1]. Conditions like erosive wear and enamel defects, including molar-incisor hypomineralization (MIH), hypomineralized second primary molar (HSPM), and dental fluorosis, are a growing concern globally [4].

Recent systematic reviews on erosive wear in children and adolescents faced challenges due to differing indices used for assessment [4]. The Basic Erosive Wear Examination (BEWE), established in 2008, is widely used but focuses solely on erosive etiology, neglecting other contributing factors like attrition and abrasion [5]. Enamel defects, such as hypomineralization, make teeth more prone to wear and accelerate early aging [4].

Enamel defects of higher prevalence have a significant impact on the oral health of affected children [1]. Understanding the current prevalence of early enamel wear in the primary dentition, caused by various etiologies such as abrasion, attrition, and acid erosion, or the combination of these factors, is crucial. Additionally, it is essential to investigate the synergistic effect of these factors on teeth with compromised mineral structure. This knowledge is of paramount importance for the development and direction of public health policies aimed at the prevention and appropriate treatment of these conditions, as well as the promotion of better oral health in the pediatric population. Currently, there is a gap in the literature regarding the precise quantification of the prevalence and the combined etiological factors contributing to early enamel wear in children, highlighting the need for comprehensive epidemiological studies to guide effective public health strategies.

The introduction of new concepts and indices is important for advancing the understanding and management of dental conditions. In this context, we present the Childhood Early Oral Aging Syndrome (CEOAS) and the associated index proposed for validation. This concept aims to unify the assessment of early enamel wear in the primary dentition by relying on observed signs and reported symptoms from patients, rather than focusing solely on isolated etiologies. The index seeks to integrate and evaluate various factors that may contribute to premature and non-physiological loss of dental structure, including both intact and hypomineralized enamel wear. The goal is to provide a more comprehensive and practical approach to diagnosing and treating early wear, considering the complex interaction of the involved factors. Thus, the proposed index may contribute to a more effective approach to identifying and managing early wear in children.

Therefore, the aim of the present study was the development and validation of a Childhood Early Oral Aging Syndrome index for the primary dentition as a diagnostic and epidemiological survey tool.

## Materials and methods

### Study design

The methods will be structured in two distinct steps. For clarity, we follow the recommendations for COSMIN (Consensus-based Standards for the selection of health Measurement Instruments).

Development of the indexContent validation by specialists2.1 Creation of the content validation form2.2 Selection of reviewers (specialists)2.3 Determination of content validity2.4 Review of items2.5 Attributing a score to each item2.6 Calculation of content validity index (CVI)

### Development of CEOAS index

The aim of the Childhood Early Oral Aging Syndrome index is to investigate clinical signs and symptoms related to the early loss of dental structure associated with the most prevalent enamel defects, which significantly contribute to oral aging. The clinical management of tooth wear is also addressed in CEOAS scores 1, 2 and 3. Current indices used for non-carious conditions do not enable the concomitant investigation of enamel defects, which makes the proposed index innovative and of extreme important to epidemiological surveys. Understanding the prevalence of factors that either separately or synergically accelerate the process of early aging is useful to the establishment of novel treatment strategies.

The CEOAS index involves scores of 0 to 3 for the assessment of tooth wear and dental management, whereas scores of I, II and III are used concomitantly in cases of the presence of enamel defects, as shown in (Table 1).

**Table 1 pone.0310543.t001:** Childhood Early Oral Aging Syndrome (CEOAS) index.

**CEOAS index**	
**CEOAS 0**	**Absence of signs**
**CEOAS 1**	**Mild:** Presence of clinical signs in reversible stages, without sensitivity. Such cases require follow-up.
**CEOAS 2**	**Moderate:** Presence of advanced signs with sensitivity and compromised function. Such cases require restorative treatment and management of the sensitivity.
**CEOAS 3**	**Severe:** Presence of severe signs with pulp involvement and the risk of the loss of the tooth. Such cases require more invasive and rehabilitative treatment.
**CEOAS I**	**Presence of PSMH–Demarcated opacities**
**CEOAS II**	**Presence of PSMH–Post-eruptive breakdown (PEB)**
**CEOAS III**	**Presence of fluorosis**

**CEOAS 0:** Absence of signs and symptoms of CEOAS.

**CEOAS 1**: Clinical findings compatible with chronological age and oral age. First clinical signs (facets with initial wear on enamel level without altering function), without symptoms. Such cases require clinical follow-up.

Due to the lack of studies on the physiological wear pattern in the primary dentition, slight tooth wear without symptoms, functional or esthetic problems compatible with physiological wear is considered in this score.

**CEOAS 2**: Signs of wear not compatible with chronological age (facets with deep wear, with dentin exposure and compromised function) and symptoms of hypersensitivity. May have gingival recession. Such cases require restorative treatment and management of the sensitivity. Due to the lack of studies on the physiological wear pattern in the primary dentition, atypical tooth wear for the age of the patient (pathological wear), with symptoms as well as functional and esthetic problems are considered in this score.

**CEOAS 3**: Signs of severe wear not compatible with chronological age, with pulp involvement (inflammation or necrosis), compromising function and the stomatognathic system. May have tooth fissures, root fissures, tooth fractures, gingival recession and changes in the temporomandibular joint. Loss of the tooth may occur. Such cases require invasive treatment (endodontic, restorative, rehabilitative or extractive).

**CEOAS I:** In the presence of primary second molar hypomineralization (PSMH) with demarcated opacities and without post-eruptive breakdown (PEB), the CEOAS I score should be recorded concomitantly with the 1, 2 or 3 score detected in the clinical examination.

**CEOAS II:** In the presence of primary second molar hypomineralization (PSMH) with post-eruptive breakdown (PEB), the CEOAS II score should be recorded concomitantly with the 1, 2 or 3 score detected in the clinical examination.

**CEOAS III:** In the presence of dental fluorosis, the CEOAS III score should be recorded concomitantly with the 1, 2 or 3 score detected in the clinical examination.

Images exemplifying the index scores are presented below. In Fig 1, CEOAS 0 (A and B) and CEOAS 1 (C and D) scores are presented. In Fig 2, CEOAS 2 (E and F) and CEOAS 3 (G and H) scores are presented. In Fig 3, CEOAS 1 associated with CEOAS I (I and J) and CEOAS 1 associated with CEOAS II (K and L) scores are presented. In images I and J, enamel defects of the type Hypomineralization of Second Primary Molars (HSPM) without post-eruptive breakdown (PEB) in tooth 65 can be observed. In images K and L, enamel defects of the type Hypomineralization of Second Primary Molars (HSPM) with post-eruptive breakdown (PEB) in tooth 55 can be observed.

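### The definitions of defect codes I, II and III leave out wear score 0, so a tooth with an enamel defect and no wear at all has no valid code

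*Protocol article*

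**What the plan says.** The section Development of CEOAS index sets up two parts of the index: scores 0 to 3 for tooth wear and its management, "whereas scores of I, II and III are used concomitantly in cases of the presence of enamel defects". Nothing in that sentence excludes score 0.

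The definitions below Table 1 are more specific:

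- Code I (hypomineralized second primary molar, opacities without breakdown): "the CEOAS I score should be recorded concomitantly with the 1, 2 or 3 score detected in the clinical examination".
- Code II (the same condition with post-eruptive breakdown): "the CEOAS II score should be recorded concomitantly with the 1, 2 or 3 score detected in the clinical examination".
- Code III (fluorosis): "the CEOAS III score should be recorded concomitantly with the 1, 2 or 3 score detected in the clinical examination".
- Score 0: "Absence of signs and symptoms of CEOAS". The text does not say whether an enamel defect alone counts as such a sign.
- Score 1: "First clinical signs (facets with initial wear on enamel level without altering function), without symptoms". The definition adds that "slight tooth wear without symptoms, functional or esthetic problems compatible with physiological wear is considered in this score".

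The worked examples in Fig 3 pair codes I and II with score 1. No example described in the text shows a defect code with score 0.

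**The concern.** The general description and the definitions do not agree on whether a defect code may stand beside score 0. The omission occurs in all three definitions, so an examiner would reasonably take it as a rule rather than a slip.

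This matters because the article presents the joint recording of wear and defects as what is new in the index, and says that "it is essential to investigate the synergistic effect of these factors on teeth with compromised mineral structure". It also wants the prevalence of factors that speed up aging, acting alone or together. To compare teeth with and without a defect, both groups must be able to show no wear. If a defect can be recorded only on a worn tooth, part of the comparison is decided by the form and not by the children.

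**Working it through.** No sample size, power or association figure in the article bears on this point, so there is nothing to reproduce. The check has two parts.

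**1. Which combinations can be coded.** Cross the wear scores (0, 1, 2, 3) with one defect entry per tooth (none, I, II, III): 4 × 4 = 16 combinations. Read literally, the definitions allow 16 − 3 = 13. The missing three are 0+I, 0+II and 0+III.

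Consider a tooth with an opacity or fluorosis and no facet:

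- Score 0 with a defect code is not provided for.
- Score 1 with a defect code does not fit, because the definition of score 1 describes wear facets.
- Table 1 words score 1 more loosely, as clinical signs at a reversible stage. If the opacity itself is taken as such a sign, the tooth becomes 1+I. Score 1 then mixes worn teeth with unworn defective teeth, although the 0 to 3 scale is described as assessing wear.

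**2. What follows for estimates.** All inputs here are assumptions, because the article gives none. Take 1,000 teeth, 10% with a defect, wear truly independent of defect (true odds ratio 1), and 30% of worn teeth at score 2 or 3. Wear prevalence is set at 30% and at 90%.

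| True counts | 30% worn | 90% worn |
|---|---|---|
| Defect: score ≥2 / score 1 / unworn | 9 / 21 / 70 | 27 / 63 / 10 |
| No defect: score ≥2 / score 1 / unworn | 81 / 189 / 630 | 243 / 567 / 90 |

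*Examiner drops the defect on unworn teeth.*
- Recorded defect prevalence: (9 + 21)/1,000 = 3%; (27 + 63)/1,000 = 9%. The truth is 10%.
- Score 0 versus ≥1: no tooth with a recorded defect has score 0, so the odds ratio is unbounded.
- Score ≥2 versus ≤1: (9 × 889)/(21 × 81) = 4.70, where 889 = 189 + 630 + 70; and (27 × 667)/(63 × 243) = 1.18, where 667 = 567 + 90 + 10. The truth is 1.

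*Examiner raises unworn defective teeth to score 1.*
- Recorded wear prevalence: (270 + 100)/1,000 = 37% instead of 30%; (810 + 100)/1,000 = 91% instead of 90%.
- Score 0 versus ≥1: again no defective tooth has score 0, so the odds ratio is unbounded.
- Score ≥2 versus ≤1: (9 × 819)/(91 × 81) = 1.00; (27 × 657)/(73 × 243) = 1.00. Moving a tooth from 0 to 1 does not cross this cut.

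*Restricted to teeth scored 1 to 3, score ≥2 versus 1.* (9 × 189)/(21 × 81) = 1.00; (27 × 567)/(63 × 243) = 1.00. Nothing is distorted.

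Over defect prevalence of 5% to 20% and wear of 30% to 90%, dropping the defect gives an odds ratio for ≥2 versus ≤1 of 1.17 to 5.17 when the truth is 1.

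**With 0+I, 0+II and 0+III allowed**, all 16 combinations can be coded and the odds ratio for any wear returns to the assumed value of 1.00.

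**The case against.** The best defence is that no sentence forbids a defect code with score 0. The restriction is inferred from three lists that omit 0, and the general description can be read as allowing it. That stands as a limit on the wording of the point, but it does not dispose of it: on that reading the two parts of the section disagree, and examiners still have no instruction for the unworn tooth.

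The gap is also narrow. Physiological wear falls in score 1, so a defect without pathological wear can be coded. Only wholly unworn teeth are affected, and if few teeth are unworn the distortion is small. In the simplified version, which keeps one worst score, a child with a defect on one tooth and wear on another can still be coded. All of this stands.

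The study described is a content validation by specialists. It estimates no association, its S-CVI/UA does not depend on the coding rule, and the specialists are invited to suggest improvements before scoring. The form gives the main purpose as the prevalence and severity of wear, not the stand-alone prevalence of defects. The later study is only sketched and might record defects separately. These points lower the urgency. However, the index is what this study delivers, and the four rating items are global and do not ask about coding rules, so a favourable rating could carry the gap forward.

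Finally, code II denotes breakdown of enamel, which may itself be regarded as loss of structure. Whether 0+II is meaningful is a fair question for the sponsor.

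**Conclusion.** The point holds in a limited form. Followed literally, the definitions leave a defect on a wholly unworn tooth without a valid code, and they do not match the general description. Whichever way the examiner resolves this, the tooth-level contrast of score 0 versus ≥1 by defect is fixed by the coding. That result needs no assumed figures. The size of the prevalence error does: it depends on how common unworn teeth are, and ranges from slight at 90% wear to substantial at 30%.

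A reader might infer that the effect of defects on wear cannot be estimated at all. The documents do not support this. The severity gradient among scores 1 to 3 is untouched, and the contrast of ≥2 versus ≤1 is distorted only if the defect is dropped. Nor do they support the inference that the content validity result is compromised. The consequence falls on the index as a survey tool and on the observational study announced at the end of the section on calculating the CVI.

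**What to change.** Reconcile the general description with the three definitions by treating wear and defect as independent axes: let codes I, II and III be recorded with 0, 1, 2 or 3, and state that score 0 means absence of wear signs and symptoms. The sponsor should also state whether post-eruptive breakdown (code II) without wear facets can take score 0.

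The scores carry management text as well, so that text must be reconciled with the recording rule. How such teeth are managed is for the sponsor to settle and is not proposed here.

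The change should be made before the specialists score the index or, failing that, at the item review step, and in any case before the observational study, because a defect that was never recorded cannot be recovered in analysis. The cost is a short edit to three definitions, a clarified score 0 and one sentence on code II. No extra data are needed.

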**Fig 1 pone.0310543.g001:**
[figure not shown]
CEOAS 0 (A and B) and CEOAS 1 (C and D) scores.

**Fig 2 pone.0310543.g002:**
[figure not shown]
CEOAS 2 (E and F) and CEOAS 3 (G and H) scores.

**Fig 3 pone.0310543.g003:**
[figure not shown]
CEOAS 1 associated with CEOAS I (I and J) and CEOAS 1 associated with CEOAS II (K and L) scores.

The CEOAS index can be used in the simplified version with the score of the greatest severity found. In the complete version, the CEOAS index can be used followed by an odontogram on which each tooth is assigned a score (Table 2).

**Table 2 pone.0310543.t002:** Odontogram for Childhood Early Oral Aging Syndrome (CEOAS) index.

Odontogram										
Tooth	55	54	53	52	51	61	62	63	64	65
Tooth	85	84	83	82	81	71	72	73	74	75

### Content validation by specialists

**Creation of content validity form**

**Table pone.0310543.t003:** 

**Content validity of Childhood Early Oral Aging Syndrome (CEOAS) index.** Dear specialists, This index was developed to provide a reliable, standardized tool for the investigation of clinical signs and symptoms related to early oral aging in childhood, with the inclusion of enamel defects, which are currently highly prevalent. The main purpose of the index is to serve as a tool for epidemiological surveys and enable knowledge on the prevalence and severity of tooth wear in the pediatric population, contributing to the planning of health actions based on the data collected. We need your specialized opinion on the degree of relevance of each item to the domains measured. Your review should be based on the relevance, clarity and applicability of the score developed for the CEOAS index, as found in Table 3. We would be grateful for verbal or written suggestions that enable us to improve the content of the index.

#### Selection of reviewers (specialists)

The selection of specialists for the assessment will be based on the individual experience of doctoral professors specializing in pediatric dentistry, who will be chosen to ensure content validity, following recommendations. Following recommendations for content validation, at least six specialists will be selected [6]. The recruitment period for specialists will take place between July 29, 2024, and September 16, 2024.

#### Determination of content validity

Content validation will not be performed in person. The online content validation form will be sent to the specialists with the items and criteria to be assessed (Table 3). A deadline for evaluation will be requested, and the entire process will be monitored. The images used to validate the Early Childhood Oral Aging Syndrome index for deciduous dentition were collected at the Dental Clinic of the Metropolitan University of Santos (UNIMES), in the Pediatric Dentistry discipline and in the Pediatric Dentistry Specialization program between April 1, 2024, and May 31, 2024. After obtaining written consent from parents or guardians, children were also informed, in appropriate language, about the objectives and procedures of the research and agreed to participate voluntarily, expressing their assent, which was recorded in the Informed Assent Form. The protocol for this study was approved by the Human Research Ethics Committee of the Metropolitan University of Santos-UNIMES (certificate number: 77036723.7.0000.5509) and the protocol registered in clinical trials (S1 File). The original research project submitted to the Research Ethics Committee, in both the original language and in English, can be found in the (S2 and S3 Files), respectively.

**Table 3 pone.0310543.t004:** Items and assessment and validation criteria of the CEOAS index.

**Items and assessment and validation criteria of the CEOAS index**				
Is the CEOAS index relevant to the diagnosis of early oral aging syndrome?	1	2	3	4
	It is not relevant.	Relevant, but needs major revision.	Relevant, but needs minor revision.	Very relevant
Is the CEOAS index clear for the diagnosis of early oral aging syndrome?	1	2	3	4
	It is not clear	Clear, but needs major revision.	Clear, but needs minor revision.	Very Clear
Is the CEOAS index relevant with regards to communication among health professionals and researchers?	1	2	3	4
	It is not relevant.	Relevant, but needs major revision.	Relevant, but needs minor revision.	Very relevant
Is the CEOAS index applicable for diagnoses and epidemiological surveys?	1	2	3	4
	It is not applicable.	Applicable, but needs major revision.	Applicable, but needs minor revision.	Very applicable

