#### Attributing a score to each item

After the review, the specialists will attribute a score to each item (Table 3) corresponding to their assessments in terms of the relevance, clarity and applicability of the content and send their assessments before the deadline stipulated for the process. To assess the content, if a specialist indicates "1" on Table 3 (Not relevant/Not clear), a discussion meeting will be held with the group of specialists. This meeting will address and clarify any doubts or issues raised, ensuring consensus and accuracy in the content evaluation.

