#### Calculation of content validity index (CVI)

The CVI will be calculated on a scale level based on the universal agreement method (S-CVI/UA). The classification of relevance should be recoded as 1 (scale score of 3 or 4) or 0 (scale score of 1 or 2). The universal agreement (UA) score is given as 1 when the item achieves 100% agreement among the specialists (only scores 3 and 4 for all items). Otherwise, the UA score is given as 0. The S-CVI/UA is equal to the sum of the UA scores divided by the number of items.

Sum of UA scores

S-CVI/UA = ______________________

Number of items

CVI values higher than 0.83 will be considered acceptable [7].

After the validation of the index, an observational study will be conducted to identify the prevalence of early wear in the primary dentition using the Childhood Early Oral Aging Syndrome index (CEOAS), and to investigate possible associated etiological factors. The study report will adhere to the STROBE guidelines for cross-sectional studies.

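### The CVI is computed over four global questions about the whole CEOAS index, so it gives no evidence on the relevance or clarity of any of the seven score definitions

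*Protocol article*

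**What the plan says.** The section on development of the index sets out seven score definitions: "The CEOAS index involves scores of 0 to 3 for the assessment of tooth wear and dental management, whereas scores of I, II and III". The Roman-numeral scores go alongside when enamel defects are present.

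The invitation on the content validity form says "We need your specialized opinion on the degree of relevance of each item to the domains measured". Its next sentence refers specialists to Table 3 for the criteria of relevance, clarity and applicability.

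Table 3 holds four questions, each on a 1 to 4 scale:

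- "Is the CEOAS index relevant to the diagnosis of early oral aging syndrome"
- "Is the CEOAS index clear for the diagnosis of early oral aging syndrome"
- "Is the CEOAS index relevant with regards to communication among health professionals and researchers"
- "Is the CEOAS index applicable for diagnoses and epidemiological surveys"

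The scoring section says that "the specialists will attribute a score to each item (Table 3"). The CVI section states "The classification of relevance should be recoded as 1 (scale score of 3 or 4) or 0 (scale score of 1 or 2"). An item gets a UA score of 1 only if all specialists give it 3 or 4. The S-CVI/UA is the sum of UA scores over the number of items, and values above 0.83 are acceptable. At least six specialists are planned.

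There is also an unscored route. Specialists review the content critically before scoring and may make verbal or written suggestions. A score of 1 leads to a group discussion meeting.

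**The concern.** Content validation of a graded index should show whether its definitions are relevant and can be understood and told apart. Here the rated units are four judgements on the whole index, so the only quantitative acceptance test says nothing about any single definition.

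The definitions give specialists real matters to judge. CEOAS 1 describes enamel-level wear without symptoms. CEOAS 2 combines dentin exposure, compromised function and hypersensitivity. Exposed dentin without sensitivity is not clearly placed by either text. Scores I to III are to be recorded with a 1, 2 or 3, and no code is stated for a defect in a tooth scored 0. A specialist who notices such a point can register it in the ratings only by shading one answer about the whole index.

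A prevalence study using the index is to follow validation, so an ambiguous definition that passes here is carried into that survey.

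**Working it through.** The protocol article gives no sample size or power figure to reproduce. The 0.83 threshold and the minimum of six specialists are taken from cited sources. The check is on what the stated formula can show.

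**Inputs.** Seven definitions (development section, Table 1); k = 4 rated items (Table 3); n = 6 specialists (selection section, minimum); S-CVI/UA = (sum of UA scores)/k, acceptable if above 0.83 (CVI section).

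**1. Ratings tied to a definition.** Total ratings are 4 x 6 = 24. The subject of all four questions is the whole index, so 0 of 7 definitions is rated.

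**2. Attainable values.** With k = 4 the S-CVI/UA can be 0, 0.25, 0.50, 0.75 or 1.00. Since 3/4 = 0.75 fails, only 4/4 = 1.00 passes.

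**3. A pass that hides a definition.** Suppose all six specialists score clarity 3 because a definition needs minor revision, not necessarily the same one. Each 3 is recoded to 1, so clarity has UA = 1. If the other three questions also receive only 3s and 4s, S-CVI/UA = 4/4 = 1.00. The index passes, and no rating identifies the definition.

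**4. A failure that does not locate the fault.** One specialist scores clarity 2. Clarity has UA = 0 and S-CVI/UA = 3/4 = 0.75, a fail. The ratings do not say which definition was meant, and the meeting is not triggered because that requires a 1.

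**5. What definition-level ratings add.** Seven definitions x 2 criteria = 14 ratings per specialist, or 14 x 6 = 84 in all. For each of the 14, I-CVI = (number of ratings of 3 or 4)/6.

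**6. Why universal agreement must be kept.** If S-CVI/Ave (the mean of the I-CVIs) replaced UA at the same threshold, two results would pass that should not:

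- One of six specialists rejects every definition: each I-CVI = 5/6 = 0.833, and the mean of 0.833 exceeds 0.83.
- One definition is accepted by one specialist and the other six by all: (1/6 + 6 x 1)/7 = 0.881, which also passes.

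**7. Effect of adding items.** Splitting the fourth question and adding a completeness question gives 4 + 1 + 1 = 6 items. Then 5/6 = 0.833 exceeds 0.83, so one item could fail and the index still pass. Pooling 14 definition ratings on their own would allow 12/14 = 0.857, with two failures.

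**The case against.** The strongest case for the plan is that its rule is demanding. Only 4/4 passes, so no criterion can compensate for another, and one specialist who finds a boundary unclear enough to score 2 on clarity fails the whole index. The invitation and the item review ask for suggestions on content, and a 1 leads to a meeting, so category problems can come to light. The form points to Table 3 for what is rated. The scores 0 to 3 are levels of one scale rather than seven independent items, and a relevance rating for absence of signs says little.

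Most of this stands, and it rules out several stronger readings that a reader might infer:

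- That a high CVI would show only that specialists like the idea. Clarity and applicability are each asked directly and must each be unanimous.
- That mixing criteria distorts the decision. Under 4/4 it cannot. The CVI section's reference to relevance alone is loose wording.
- That the form contradicts Table 3. Read together, an item is a Table 3 row, although the phrase about each item and the domains fits four global questions poorly.
- That a specialist who accepts only one use in the fourth question has no answer. Scores 2 and 3 and comments are available, but the rating will not show which use was in doubt.
- That missing content cannot be reported. It can be in comments, though no rated question asks about it.

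What the objection does not reach is the measurement itself. Comments and the meeting are unscored, have no acceptance criterion and do not enter the CVI. A strict rule on global questions remains global.

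**Conclusion.** The concern holds for what the CVI can show. Zero of seven definitions receives a rating; a value of 1.00 is compatible with a definition that every specialist would revise slightly, and a value of 0.75 does not say where the fault lies. It does not follow that the validation is empty or that category problems must go unnoticed, given the unanimous rule and the planned review. Severity: should fix.

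This rests on Table 3, the scoring section and the CVI formula as printed, which fix the rated items and the denominator, so it is not a detail left to another document. The counts of 24 and 84 ratings assume the minimum panel of six. The choice of two criteria per definition is a proposal and not taken from the protocol.

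**What to change.** Keep the four global questions and the existing S-CVI/UA rule. On the same online form and 4-point scale:

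1. Add a relevance and a clarity rating for each of the seven definitions.
2. Report the I-CVI for each definition and criterion. Revise and re-rate any definition that does not reach universal agreement (all ratings 3 or 4). Do not replace UA with S-CVI/Ave.
3. Split the fourth question into diagnosis and epidemiological surveys, and add one question on whether the categories cover all relevant signs and defects.
4. If the added questions count as rated items, state that every rated item must reach universal agreement, rather than relying on 0.83.

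**Cost.** About 14 more ratings per specialist, plus the two extra questions, with the same panel. The chance that some definition is sent back also rises. As an illustration, assume six independent specialists who each give 3 or 4 with probability 0.95 or 0.98, figures that are not in the protocol. One rating item then reaches universal agreement with probability 0.95^6 = 0.735 or 0.98^6 = 0.886. Of 14 items, 14 x 0.265 = 3.7 or 14 x 0.114 = 1.6 would be expected to fall short. A second rating round should therefore be allowed for in the timetable.
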